# The effect of daily consumption of different doses of fortified Lavash bread versus plain bread on serum vitamin-D status, body composition, metabolic and inflammatory biomarkers, and gut microbiota in apparently healthy adult: study protocol of a randomized clinical trial

**DOI:** 10.1186/s13063-019-3852-z

**Published:** 2019-12-27

**Keywords:** Vitamin D, 25(OH) D, Fortified bread, Fortification, Vitamin-D deficiency, Fortified food

## Abstract

**Background:**

Due to the high prevalence of vitamin-D deficiency worldwide and its health consequences, intervention studies at the community level are warranted. The present study has been conducted to evaluate the effectiveness of vitamin-D-fortified bread on serum vitamin-D levels, inflammatory and metabolic biomarkers, and gut microbiota composition in vitamin-D-deficient individuals.

**Methods/design:**

A double-blind, randomized controlled clinical trial is conducted on apparently healthy individuals with vitamin-D deficiency. The random allocation is done to divide participants into intervention groups including daily intake of vitamin-D-3-fortified bread (FB) with 500 IU/100 g bread (*n* = 30), FB with 1000 IU/100 g bread (*n* = 30), and 100 g plain bread (PD) (*n* = 30). At baseline and after 3 months of the intervention period, blood, stool, and urine samples are taken. Anthropometric measures, body composition, blood pressure, and dietary assessment are made. The gut microbiome composition is measured by the 16S rRNA approach. Data is analyzed by SPSS software version 21.

**Discussion:**

This study may partly explain for the first time the conflicting results from recent critical and systematic reviews regarding the role of vitamin D in microbiota composition.

**Trial registration:**

Iranian Registry of Clinical Trials (IRCT), ID: IRCT20170812035642N3. Registered on 11 March 2018; http://www.irct.ir/user/trial/28134/view.

## Background

Vitamin-D deficiency is one of the most important public health concerns worldwide. According to epidemiological maps in many parts of the world, about half of the population has insufficient serum levels of vitamin D due to insufficient exposure to sunlight and lack of dietary intake [1]. According to recently published data from Iranian National Food and Nutrition Surveillance, over 90% of the Iranian population have an undesirable serum level of vitamin D [2]. Vitamin D was taken into consideration because of its role in calcium-phosphorous and bone metabolism [3]. Thereafter, it became clear that inadequate vitamin D is associated with numerous pathological conditions such as autoimmune diseases like multiple sclerosis [4], type 1 diabetes [5], cancer [6], and even infectious diseases [7, 8]. The role of vitamin D in many tissues is known by its specific receptor, vitamin-D receptor (VDR). For example, the presence of VDR in immune system cells reflects the role of vitamin D in intestinal homeostasis and immunity [9].

The human gut is host for more than 10^14^ microorganisms, which are known as intestinal microbiota. These microorganisms play an effective role in obtaining nutrients, producing vitamins and destroying toxins by coexistence with the host [10, 11]. The intestinal microbiota is also effective in controlling pathogens [12], regulating intestinal immunity [13], and host metabolism [14, 15]. Based on previous studies, some of the factors affecting microbiome colonization, includes diet [16–18], host genetics [19], the environment [20], and medications such as antibiotics and laxatives [21].

Recently, a hypothesis has been suggested that vitamin-D deficiency can alter the composition of intestinal bacteria. A recently published observational study has shown a link between dietary intake of vitamin D and intestinal bacteria [22]. In mouse models, it has also been observed that vitamin D can alter the intestinal microbiota population into a beneficial bacterium [23]. It also seems that vitamin D plays a role in regulating the immune system in the gut, and its deficiency may change the function of the intestinal wall, leading to transfer of endotoxins, like lipopolysaccharides (LPSs), into the bloodstream, which itself causes the development of inflammation [24]. Animal studies have also shown that vitamin D reduces dysbiosis, infection, permeability of the intestinal epithelial duct and ultimately deacreases the incidence of inflammatory bowel diseases, like Crohn’s disease, by maintaining the hemostasis of the intestinal epithelium cells and tight-junction structures [23, 25, 26].

Vitamin D level is largely dependent on exposure to ultraviolet sun rays (wave-length of 290–315 nm). However, various environmental, cultural, social, and individual factors can affect the amount of ultraviolet B (UVB) that reaches the skin. On the other hand, dietary sources of vitamin D are too rare. Therefore, supplementation and fortification are the only ways to achieve the amount of vitamin D required. Supplement consumption is challenged because of population coverage, people’s compliance, cost, and regular consumption of supplements [27]. In contrast, using fortified foodstuffs has the advantage of lower cost and higher compliance [28]. Then, vitamin-D fortification seems to be a better startegy to prevent or treat vitamin-D deficiency. In this study we will fortify bread with vitamin D, because it is available to people with moderate to severe food-insecurity households and its use is not significantly related to socioeconomic factors such as income and education. Also, according to the latest survey of the national food pattern in Iran, the average consumption of bread is more than 300 g per day,while milk intake,another current food that is fortified, is only 38 g per day [29]. In addition, bread is a staple food which is consumed routinely in all meals by the Iranian population.

Considering the high prevalence of vitamin-D deficiency in Iran [30], and its contribution to chronic diseases [31], using a fortified food, such as vitamin-D3-fortified bread, if proved to be effective in this study, can be encouraged as a preventive tool. Moreover, studies on the role of vitamin D in the human intestinal microbiota are rare. Therefore, this study has been designed to test the effectiveness of vitamin-D-fortified bread on serum vitamin-D levels, inflammatory and metabolic biomarkers, and gut microbiota composition in vitamin-D-deficient individuals.

### Specific aim

The main aim of this study is to determine the effect of daily consumption of vitamin-D3-fortified bread on serum vitamin-D status, body composition, metabolic and inflammatory biomarkers, and gut microbiota in apparently healthy adults.

#### Primary objective

To compare within- and between-group variations in circulating 25(OH) D levels.

#### Secondary objectives

To compare within- and between-group variations in anthropometric, metabolic, inflammatory and oxidative stress biomarkers and gut microbiota

#### Hypotheses

Daily consumption of vitamin- D3-fortified -bread improves serum 25(OH) D levels in apparently healthy subjects.Daily consumption of vitamin- D3-fortified -bread improves the biomarkers of anthropometric, metabolic, inflammatory, and oxidative stress and gut microbiota in apparently healthy subjects.

### Methods/design

#### Design

This is a 3-month, double-blind, randomized controlled clinical trial (RCT) in which apparently healthy subjects aged 20–60 years are enrolled (Fig. 1).

**Fig. 1 Fig1:**
[figure not shown]
CONSORT flow diagram

#### Ethics, consent, and permissions

Tehran University of Medical Sciences will provide financial support for the current project. The trial will be conducted in compliance with the Declaration of Helsinki. The trial has received ethical approval from the Ethics Committee of Tehran University of Medical Sciences (number 96–02–161-35097). The current protocol is version 1, dated 31 January 2017, and any changes to the protocol will be communicated to all relevant parties, including participants.

#### Participant recruitment

In this trial, we will recruit a total of 90 participants (each group 30 subjects) from apparently healthy subjects of Tehran, the capital city of Iran. Participant recruitment was expected to commence by September 2018, and the trial is due to last 20 months. This assumes 4 months for participants recruitment, 4 months for run-in periods and intervention, 2 months for laboratory testing, 2 months for data collection, preparing and entering into SPSS software, 3 months for data retrieval and analysis, and 4 months to write the study report. A Standard Protocol Items: Recommendations for Interventional Trials (SPIRIT) Checklist [32] was used to report this protocol (Additional file 1, SPIRIT Checklist). Table 1 also shows the trial schedule. Before collecting any information, informed consent will be obtained from all participants. After reviewing the consent forms and answering any probable questions by study staff, those who are interested will be asked to sign the forms. A copy of the consent form will be gave to participants and all original signed consent forms will be kept by the study staff (Additional file 2, consent form).

**Table 1 Tab1:**
[figure not shown]
Timetable of protocol

*ALT* alanine aminotransferase, *AST* aspartate aminotransferase, *BMI* body mass index, *CBC* complete blood cell count*, FBS* fasting blood sugar, *HDL-C* high-density lipoprotein cholesterol, *LDL-C* low-density lipoprotein cholesterol, *TG* triglycerides, *WHR* waist to hip ratio

#### Eligibility

The inclusion criteria for subjects include (1) having vitamin-D deficiency (< 50 nmol/L), (2) no intake of supplements containing vitamin D or fish oil during the last 3 months, (3) not having clinical signs of diseases that interfere with vitamin-D metabolism (liver and kidney disease), and (4) not receiving any medications that interfer with the metabolism of vitamin D (corticosteroids, estrogen). Exclusion criteria include (1) any disease, or the need to use medication, which interferes with vitamin-D metabolism, (2) pregnancy or breastfeeding, and (3) any weight-loss treatments. Research participants can leave the study whenever they want.

#### Setting

The subjects will be recruited from the community by advertisements and notices, advertisements posted in public places, etc. For those who are interested in participating in the trial, study staff will confirm potential interest and eligibility of volunteers. Then, they will be reffered to a laboratory to identify subjects with vitamin-D deficiency. If they have the requirement criteria and express an interest to collaborate in the study, the appointment will be set for their first visit. At the first visit, the potential participants will have the proposals of the research project fully explained to them, and all interested participants will be asked to fill in the consent form. A general information questionnaire, including demographic information, disease history, type and amount of medicine used, occupation, smoking status, a sun-light exposure questionnaire, Physical Activity Questionnaire (PAQ), and a food recall questionnaire will be completed for each participant.

#### Sample size

Based on data on serum 25(OH) D changes from Nikooyehet al [33]., to achieve 20 nmol/L difference in circulating 25(OH) D with a two-sided alpha of 0.05 and a beta of 0.2 after a 12-week intervention period, the target sample size will be 30 individuals per treatment group. We are not adjusting the primary outcome comparisons for the multiple pairwise comparison.

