#### Randomization/blinding

Those participants with vitamin- deficiency (< 50 nmol/L) will be randomly assigned to receive either vitamin-D-fortified breads or plain bread. Randomization will be done using a computer-based random-digit generator. The allocation will be done in a 1:1:1 ratio. The research team, all participants, the staff involved in the clinical center, and those assessing the outcomes and analyzing the data will be blinded to group assignment. Letter codes A, B, and C wil be used to identify the three groups, respectively. Breads will be packaged in identical color, size, and taste. Therefore, neither the participants nor the researchers, the interviewers or laboratory staff know which participants belong to which group,

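### The stated 80% power covers only a pair of arms that truly differs by 20 nmol/L, with 30 evaluable per arm and an unadjusted 0.05; the planned recruitment and Bonferroni test do not secure those conditions

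*Protocol article*

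**What the plan says.** All references are to the protocol article.

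- **Sample size.** Drawing on a cited study of changes in serum 25(OH)D, the plan sets 30 per group "to achieve 20 nmol/L difference in circulating 25(OH) D with a two-sided alpha of 0.05 and a beta of 0.2", and concludes that "the target sample size will be 30 individuals per treatment group". It states neither the SD nor the pair of arms to which the 20 nmol/L refers. The same section says that the primary outcome comparisons are not adjusted for multiple pairwise testing.
- **Participant recruitment.** The plan says "we will recruit a total of 90 participants (each group 30 subjects", which is the calculated number with nothing added.
- **Eligibility.** "Research participants can leave the study whenever they want".
- **Randomization/blinding and Intervention.** There are three arms (plain bread, 500 IU/100 g and 1000 IU/100 g) over 12 weeks. "The allocation will be done in a 1:1:1 ratio".
- **Statistical analyses.** Change within groups is tested by paired t tests. Repeated-measures ANOVA is used for time and time-by-group effects. Groups are compared by ANOVA with Bonferroni post-hoc tests.

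**The concern.** A single difference, alpha and beta are given for a trial with three arms and therefore three possible pairwise comparisons. A reader will tend to apply the 80% to each of them. It applies to a given pair only under three conditions, and the rest of the article leaves each one open:

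1. The pair truly differs by 20 nmol/L. The section does not say which pair this is.
2. Thirty per arm contribute to the analysis. Exactly 30 per arm are recruited, withdrawal is free, and the planned paired and repeated-measures tests need both a baseline and a final value.
3. The test is run at an unadjusted 0.05. The Statistical analyses section plans Bonferroni instead, which contradicts the Sample size section.

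What is at stake is how a non-significant result is read. If the power is taken as 80% when it is really nearer two-thirds, or about 30% for a modest step between doses, an inconclusive comparison may be given too much weight.

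**Working it through.** **Inputs from the article.** Difference 20 nmol/L, two-sided alpha 0.05, power 0.80, n = 30 per arm (Sample size); 90 in total (Participant recruitment); equal allocation (Randomization/blinding); Bonferroni post-hoc tests (Statistical analyses). Three pairs give a per-pair alpha of 0.05/3 = 0.0167.

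**Input not given: the SD.** The stated n = 30 therefore cannot be reproduced, only inverted.

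- Normal formula, n = 2(1.960 + 0.842)² SD²/20². Setting n = 30 gives SD = 20 / (2.802 × √(2/30)) = 27.6.
- Noncentral t with 58 df: n = 30 and 80% power require a standardised difference of 0.7356, so SD = 20/0.7356 = 27.2.

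An SD of about 27 is thus what the plan implies if 30 is the exact minimum. That is an assumption, so a range of SDs is shown below.

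**Formula for power.** Two-sample t test with noncentrality δ/(SD·√(2/n)) and 2n − 2 df. Example: δ = 20, SD 27.19, n = 27 gives 20/(27.19 × 0.2722) = 2.70, and power 75.6%.

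**Power for a true 20 nmol/L difference**

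| SD | 30 per arm, alpha 0.05 | 27 per arm (10% loss) | 24 per arm (20% loss) | 30 per arm, alpha 0.0167 |
|---|---|---|---|---|
| 24 | 88.8% | 85.2% | 80.7% | 77.4% |
| 27.19 | 80.0% | 75.6% | 70.4% | 65.0% |
| 30 | 71.9% | 67.2% | 61.8% | 54.9% |

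At SD 27.19, Bonferroni with 10% loss gives 59.3%.

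**How the three differences relate.** (500 IU − plain) + (1000 IU − 500 IU) = (1000 IU − plain). If the 20 nmol/L is the difference between 1000 IU and plain bread, at least one of the two adjacent steps is 10 nmol/L or less. For all three pairs to reach 20 in the direction of dose, 1000 IU must exceed plain bread by at least 40.

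**Power for a 10 nmol/L step, 30 per arm**

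| SD | alpha 0.05 | alpha 0.0167 |
|---|---|---|
| 20 | 47.8% | 30.7% |
| 24 | 35.5% | 20.6% |
| 27.19 | 28.8% | 15.8% |
| 30 | 24.6% | 12.8% |

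No SD in this range brings a 10 nmol/L step near 80%.

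**The case against.** **The SD is not in the article.** Using a value back-solved from n = 30 to show that there is no slack is circular. This objection stands. At SD 24, 24 completers per arm still give about 81%, so 30 may contain slack or an unstated allowance. The percentages for loss are therefore conditional. What remains is that the text ties 30 directly to the 80% and recruits exactly that number.

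**A reader might infer that 80% cannot hold for all three pairs, or holds only with zero dropout.** The article supports neither reading. It claims power for a pair that differs by 20, not joint power across the three pairs, and arm means spaced 0/20/40 would give every pair about 80% or more. The zero-dropout reading requires 30 to be the exact minimum, which cannot be shown.

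**Retention may be good.** A two-week run-in, described before randomization, tests motivation, and visits are every two weeks. Losses in the run-in may therefore not thin the arms. This is fair, but it does not cover withdrawal during the 12 weeks of intervention.

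**No hypothesis of superiority or equivalence between the two doses is stated.** The title sets the fortified breads against plain bread. This also stands: the 10 nmol/L step is an illustration, and the article makes no equivalence claim. It matters because the pairwise comparisons are called primary and the target pair is not named.

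**A condensed article may leave the SD and the dropout allowance to the full protocol.** That is accepted, and neither omission is the point by itself. The conflict between no adjustment and Bonferroni is within the article. The planned covariance analysis could raise power somewhat, but no correlation is given from which to estimate by how much.

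**Conclusion.** The point holds in a limited form. No arithmetic error is shown in n = 30; without the SD it can be neither confirmed nor refuted. The fault is that the 80% is stated without the conditions on which it depends, and one of them, the unadjusted alpha, is contradicted by the article's own analysis section.

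- **Loss.** If 30 is the bare minimum (SD about 27), power falls from 80% to about 76% at 10% loss and 70% at 20%. At SD 24 it stays at about 85% and 81%.
- **Alpha.** Under Bonferroni with no loss, power is about 65% at SD 27 and 77% at SD 24, below 80% at both.
- **Smaller dose step.** For 10 nmol/L, power is about 25% to 48% over SDs from 30 down to 20, before any adjustment.

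These figures assume a two-sample t test, equal arms and equal loss across arms. The SDs and loss rates are assumptions, not figures from the article.

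**What to change.** Keep 90 participants and revise the Sample size section as follows:

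1. Name the pair of arms to which the 20 nmol/L refers.
2. State the SD taken from the cited study. The back-solved 27 should not be written in as if it were a design input.
3. Restate the power, with that SD, for the number expected to complete.
4. Settle whether the primary comparisons are adjusted, make the Sample size and Statistical analyses sections agree, and give the power at the alpha actually used.
5. Add that the 80% does not extend to a difference between 500 IU and 1000 IU smaller than 20 nmol/L.

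A linear dose-trend test would not help. With equally spaced doses and equal arms its contrast is (−1, 0, 1), which is the comparison of 1000 IU with plain bread again.

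The cost is wording and a short recalculation, with no extra participants. The restated power may be less favourable than 80%.

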### Statistical analyses

Data analysis will be done using SPSS version 21 software. To describe the quantitative data, the mean and standard deviations will be used and to describe the qualitative data absolute and relative abundance will be used. To compare absolute or relative abundance the chi-square or Fisher’s exact statistics will be used. As the data should compare groups, between groups, and between-group changes, and to reduce the probability of the error, an analysis of two-way variance with repeated measures will be used to explore the impact of time and time-group effects with adjustment using the Bonferroni post-hoc test. The effects of the intervention in each group were examined using the paired *t* test versus the baseline values. Between-group comparisons were examined using analysis of variance (ANOVA) followed by a Bonferroni post-hoc analysis. Covariance analysis will be used to adjust the effects of confounding variables. The correlation between the three groups will be evaluated by Pearson (normal data distribution) or Spearman (abnormal distribution). The significance level in this study will be considered to be *p* < 0.05.

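### The sample-size section leaves the primary pairwise comparisons unadjusted while the analysis section Bonferroni-adjusts them, so 25(OH)D has two decision rules and the stated 80% power fits only one

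*Protocol article*

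**What the plan says.** The Sample size section of the protocol article sizes the trial "to achieve 20 nmol/L difference in circulating 25(OH) D" "with a two-sided alpha of 0.05 and a beta of 0.2 after a 12-week intervention period", and concludes that "the target sample size will be 30 individuals per treatment group". The variability is taken from a cited earlier study and no SD is given. The section ends: "We are not adjusting the primary outcome comparisons for the multiple pairwise comparison".

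The Statistical analyses section says: "Between-group comparisons were examined using analysis of variance (ANOVA) followed by a Bonferroni post-hoc analysis". It also describes a two-way repeated-measures analysis of variance "with adjustment using the Bonferroni post-hoc test". Neither sentence separates 25(OH)D from the other outcomes.

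The Primary objective section covers within-group and between-group comparison of circulating 25(OH)D, and there are three arms (Randomization/blinding: "The allocation will be done in a 1:1:1 ratio"). There are thus three possible pairwise comparisons on the primary outcome.

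**The concern.** The two sections give different rules for the same tests. Under the first, each 25(OH)D pair is judged at 0.05. Under the second, read as Bonferroni over three pairs, each is judged at 0.05/3 = 0.0167. A pair with unadjusted p = 0.03 is a success under the first rule; under the second its adjusted p is 3 × 0.03 = 0.09 and it fails. Whoever analyses the trial could follow either rule after seeing the data and cite the protocol for it.

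The power statement is tied to the first rule only. If the second is the one carried out, the stated beta of 0.2 is not delivered at 30 per group.

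This is not a detail left to an unseen analysis plan. The article states both rules, and an analysis plan could follow one only by departing from the other.

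**Working it through.** **Inputs.** From the Sample size section: difference 20 nmol/L, two-sided alpha 0.05, power 80%, n = 30 per group. From Randomization/blinding: three equal arms, so three pairs. The SD is not given and is back-solved below; that is an assumption.

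**1. The plan's own figure.** Without an SD, 30 per group cannot be reproduced independently. The SD that makes it exactly right is

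- normal approximation: SD = 20 / [(1.960 + 0.842) × √(2/30)] ≈ 27.6 nmol/L;
- two-sample t test (noncentral t, 58 df): 27.2 nmol/L;
- pooled three-arm error (87 df): 27.3 nmol/L.

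**2. Power if Bonferroni governs.** Taking 80% at 0.05 as given, the normal approximation does not need the SD:

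- three pairs, alpha 0.0167, critical value 2.394: Φ(1.960 + 0.842 − 2.394) = Φ(0.408) ≈ 65.8%;
- two pairs against plain bread, alpha 0.025, critical value 2.241: Φ(0.56) ≈ 71%.

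By t test, three pairs give 65.0% (58 df) or 65.3% (87 df); two pairs give 70.7% or 70.9%.

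**3. What 80% would take over three pairs.** By t test at SD 27.2, the difference detectable with 80% power at 30 per group is 23.3 nmol/L. To keep 20 nmol/L, 40 per group gives 79.8%, so 41 per group (123 in total) are needed. Adjusting for two pairs would need 37 per group.

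**4. Sensitivity to the unstated SD.** Power for 20 nmol/L at 30 per group (t test, 58 df):

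| Assumed SD (nmol/L) | Alpha 0.05 | Alpha 0.05/3 |
|---|---|---|
| 20 | 97% | 92% |
| 24 | 89% | 77% |
| 26 | 83% | 70% |
| 28 | 78% | 62% |

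If 30 contains an unstated dropout allowance and 27 evaluable per group was the real requirement, Bonferroni power (normal approximation, three pairs) is 66% with 27 and 71% with all 30.

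**5. Error rate if no adjustment governs.** In 200,000 simulated trials with three equal arms of 30, at least one of the three unadjusted pairs is significant at 0.05 in about 12% of trials. If pairs are examined only after a significant three-arm F test, the rate is 5.0%. With one arm shifted by 20 nmol/L, the one remaining true null pair is rejected in about 5% of trials.

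**6. Power with the F-test gate.** At SD 27.2, a pair that truly differs by 20 nmol/L is declared significant in about 70% of trials when the third arm lies midway between the two, and in about 76% when the third arm equals one of them.

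**The case against.** The sections can be reconciled. The sample-size sentence is specific to the primary outcome, and the analysis paragraph is generic and covers many secondary outcomes. If the specific governs the general, 25(OH)D is tested unadjusted, Bonferroni applies elsewhere, and the power stays at 80%. That reading is reasonable, and it is why the loss of power is conditional. It does not remove the conflict, because the analysis section makes no exception and 25(OH)D is itself compared between groups.

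A reader might infer that the trial is simply underpowered at 65%. The documents do not support that. The figure needs three things: the analysis section governs, all three pairs are adjusted, and 30 per group gives exactly 80% at 0.05. The SD is not stated, and with a smaller one power stays higher even under Bonferroni. The covariance analysis that the article mentions could also raise power.

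A reader might equally infer that the no-adjustment rule means a familywise error of 12%. That is the ungated case only. The article puts an ANOVA before the pairwise tests, and with exactly three arms a significant F test as gate holds the familywise error at about 5%. The article does not say that the F test is a gate, so neither figure is established.

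The last objection is to imposing a fixed testing order, since the article states no hierarchy among the comparisons. This stands: a fixed sequence is one option, not the required remedy.

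**Conclusion.** The contradiction is real and concerns the decision rule for the primary outcome: unadjusted pairwise p-values between 0.0167 and 0.05 have no settled interpretation. The size of the consequence depends on which section is meant.

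- If Bonferroni is meant, the stated 80% is wrong as written. It becomes about 65% over three pairs (about 71% over two), with a detectable difference of about 23.3 nmol/L at 80% power over three pairs. These figures rest on the back-solved SD of about 27.2 nmol/L, that is, on 30 per group giving exactly 80% at 0.05.
- If no adjustment is meant, the power statement stands. Familywise error over three pairs is then about 12%, or about 5% if the pairs are gated on the F test, and the article does not say which.

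**What to change.** State one rule for 25(OH)D in both sections, by dated amendment before unblinding. Two routes are open.

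(a) Keep Bonferroni. Delete the no-adjustment sentence from the Sample size section and restate the power there as about 65% for 20 nmol/L over three pairs (detectable difference about 23.3 nmol/L at 80% power), replacing the back-solved SD with the one actually used.

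(b) Exempt 25(OH)D from Bonferroni in the Statistical analyses section and name a procedure that controls familywise error at 0.05. Two choices:

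- Test pairs at 0.05 only if the three-arm F test is significant. At the back-solved SD, power for a 20 nmol/L pair is then about 70 to 76%, depending on the third arm.
- Prespecify a fixed sequence, each step at 0.05 and stopping at the first non-significant result. This keeps 80% for the first comparison only; later ones are conditional on it. For example, if both fortified arms truly exceed plain bread by 20 nmol/L and the two comparisons with plain bread come first, both succeed in about 69 to 70% of trials. The sponsor would have to justify the order, since the article gives none.

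Either route is a change of wording and needs no further participants, visits or assays. Timing is the constraint: recruitment was planned for 2018 and the article is dated December 2019, so the amendment should record that it was made without knowledge of results by arm.
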